#### Ward care

Patients allocated to ward care (WC) are transferred to the surgical ward with a protocol-based discharge note using a standard form (Additional file 5: Anaesthetist - discharge note). Patients are thoroughly evaluated before transfer, and a written plan of treatment and monitoring for the first 24 h in the ward is outlined in the medical chart. Otherwise, surgical ward treatment is as standard for the individual ward. In general, the participating surgical wards have the resources and facilities to meet the monitoring and treatment levels outlined in Table 2. This level can only be exceeded for a short time, and it is not possible to initiate continuous monitoring of vital signs. If patients deteriorate they are transferred to an intermediate care, or intensive care unit to be treated appropriately.

**Table 2 T2:** Surgical ward care: an overview of facilities

**Observation**	**Monitoring level**	**Treatments goals^a^**	**Comments**
Level of consciousness	Every 8 h	GCS: 15	
Respiratory rate	Every 8 h	RR: 10 to 20	
Oxygenation	Every 8 h	SpO_2_ ≥94%	Continuous pulse oximetry is not available
Blood pressure	Every 8 h	MAP: 65 to 110 mmHg	
Heart rate	Every 8 h	HR: 50 to 100	Continuous ECG is not available. Diagnostic ECG on indication. If arrhythmia or ischaemia is detected the treatment goals are adjusted to current recommendations
		No ischaemia	
Diuresis	Every 8 h	≥0.5 mL/kg/h	
Temperature	Every 8 h	36°C to 38°C	
Pain Visual Assessment Score	Every 8 h	VAS: 0 to 2 during rest Epidural: Able to move both legs	
Central venous pressure	Not available		
Central venous oxygen saturation	Not available		
Standard blood samples	Every 24 h	Within normal reference values	Hgb ≥4.5 mmol/L
			Hgb ≥6.0 during sepsis or heart disease
**Treatment****(if needed)**	**Maximal treatment level**	**Treatments goals**	**Comments**
Infusion of sympathomimetic drugs	Not available		
Oxygen therapy on open air systems	Continuously	SpO_2_ ≥94%	Unless contraindicated. Oxygen therapy is discontinued when oxygenation is above ≥94% without oxygen therapy. During nights: minimum 2 L supplemental oxygen is given
Positive Expiratory Pressure (PEP) therapy	Assistance to PEP therapy: every fourth hour during day and evening shift	SpO_2_ ≥94%	If the patient does not need assistance with PEP therapy, guidance in self-administration of PEP therapy is available
Non-invasive ventilation	Not available		
Volume / Fluid therapy	Continuously	Systolic blood pressure: ≥100 mmHg	Fluid balance: Evaluation frequency in accordance with monitoring level and vital signs
		Diuresis: ≥12 mL/kg/day	

During evening and night shifts: Resident in surgery on in-house duty and staff specialist in surgery on call. Staff specialist in anaesthesiology/intensive care medicine on call from in-house duty.

^a^All treatment goals are adjusted to the individual patient’s co-morbidities, physiological status and in the event of complications in agreement with current recommendations.

### Baseline data

After inclusion we register the following demographic characteristics: dementia; previous stroke; chronic obstructive pulmonary disease; previous pulmonary embolism; previous myocardial infarction; chronic kidney dialysis; cancer; tobacco habit; alcohol consumption; assistance with personal hygiene; The American Society of Anaesthesiologists’ Physical Status Classification (ASA) score, and the postoperative sepsis score: grade 0, no sepsis and no systemic-inflammatory-response-syndrome (SIRS); grade 1, SIRS; grade 2, sepsis; grade 3, severe sepsis; and grade 4, septic shock [35]. We collect the following perioperative data: nature and duration of surgery; method of anaesthesia; location and duration of post-anaesthesia care; infusion of sympathomimetic drug (yes/no); blood loss; volume of crystalloid and/or colloid infusion; and infusion of blood products (type and number of units).

### Intervention period data

We measure compliance with the trial protocol by registering the frequency of observations of the measures listed in Table 3, made during the 48 h intervention period. Additionally, we register the following measures regarding level of treatment and monitoring in both groups: early-warning-score system [36] monitoring for >24 h (yes/no); nutrition initiated within 24 h (yes/no); mobilisation within 24 h of surgery (yes/no; level); mobilisation within 48 h of surgery (yes/no; level); intensivist or anaesthetist evaluation (number; specialist/non-specialist), and surgeon evaluation (number; specialist/non-specialist). Additionally, we register the use of diagnostic imaging: chest X-ray; lung scintigraphy; and echocardiography. In the IC group we register reason for: premature or late transfer to the surgical ward (respectively before or after 48 h intervention); ‘step-up’ to an intensive care bed; the Simplified Acute Physiology Score (SAPS) II [37]; the Sequential Organ Failure Assessment (SOFA) score (day 1 and 2) [38]; and the sepsis score (day 2).

**Table 3 T3:** Compliance with trial protocol

**Measures**	**IC Group (day 2)^a^**	**WC Group (day 14)^a^**
**Actual monitoring level**		
Level of consciousness (number of registrations)	x	x
Respiratory rate (number of registrations)	x	x
Continuous pulse oximetry (yes/no)	x	x
Blood pressure (number of registrations)	x	x
Continuous ECG monitoring (yes/no)	x	x
24-h diuresis (number of registrations)	x	x
Hourly diuresis registration for >24 h (yes/no)	x	x
Temperature (number of registrations)	x	x
Pain Visual Assessment Score (no. of registrations)	x	x
Central venous pressure (number of registrations)	x	x
Central venous oxygen saturation (number of samples)	x	x
Standard blood samples (number of samples)	x	x
**Treatment level**		
Infusion of sympathomimetic drugs (yes/no)	x	x
Parallel infusion of sympathomimetic drugs (yes/no)	x	x
>2 L supplemental oxygen during nights (yes/no)	x	x
Assistance to PEP therapy (number of treatments)	x	x
Non-invasive ventilation (yes/no)	x	x
Invasive ventilation (yes/no)	x	x
Emergency dialysis (yes/no)	x	x
24-h fluid balance calculation (number of registrations)	x	x
Protocol-based discharge by anaesthetist (yes/no)^b^		x
Protocol-based round by intensivist (number)	x	
Protocol-based round by surgeon (number)	x	
Patient location (hours)^c^	x	x

Data stem from medical charts, nurse charts and observation charts used in the 48-h intervention period.

^a^Timing of registration of compliance to protocol in the case report form.

^b^Registered by the anaesthetist writing the discharge note and checked at day 14.

^c^Post-anaesthesia care unit; intermediate care bed; intensive care bed; surgical ward; medical ward; and/or coronary care unit.

### Follow-up

Mortality data will be retrieved from The Danish Civil Registration System (CRS) [39]. The CRS contains mortality data on all Danish citizens, through a unique personal identification number. The retrieval from CRS will be made by an independent data manager at Copenhagen Trial Unit at interim analysis and at day 30 after the last patient has been enrolled. The secondary outcome measures are registered from the medical chart at day 30 postoperatively, and from the National Patient Registry (NPR), which contains data on hospitalisation of all Danish citizens [40]. Furthermore, return to operating theatre, and postoperative medical and surgical complications requiring treatment within 14 days of randomisation, are retrieved from the medical chart at day 30.

### Outcome measures

The primary outcome measure is all-cause 30-day mortality.

Secondary outcome measures are: (1) all-cause mortality within the total observation time, measured 30 days after the last included patient; (2) admission to an intensive care unit, and duration thereof, within 30 days of randomisation; and (3) duration of hospitalisation postoperatively (days).

### Data collection and trial conduct

Data are collected on printed case report forms, on which a unique barcode number is printed to eliminate the possibility of duplication of the case report forms. Case report forms are scanned into the database using the Verity Teleform® system (Verity, Sunnyvale, CA, USA) managed by Copenhagen Trial unit. Mortality data is extracted from The CRS. The Steering Committee will not have access to the dataset until the trial has been completed. The InCare trial is conducted in compliance with the Helsinki Declaration, and is approved by the Copenhagen Capital Region Ethical board (H-3-2010-010) and the Danish Data Protection Agency (HEH.afd.I.750.16-18). The trial is registered at clinicaltrials.gov (NCT01209663), and conducted and monitored in accordance with the ICH-GCP guidelines. Case report forms are checked for validity and internal consistency through trial site visits by Good Clinical Practice (GCP) monitors, who checks source data in approximately 10% of the case report forms selected at random. The trial is designed in compliance with the Consort Statement, and the two extensions: ‘Improving reporting of pragmatic trials’ and ‘Extending the consort statement to randomised trials of nonpharmacologic trials’ [41-43].

### Interim analyses

We have established an independent Data Monitoring Committee (DMC) to evaluate safety and efficacy on scheduled interim analyses of 30-day mortality data. The monitoring plan is based on the modified Haybittle-Peto boundaries for stopping trials after interim analyses in the second half of the inclusion period [44,45]. The mortality data are presented to the DMC under a blinded code for allocation group. The first interim analysis will be conducted when 30-day mortality data of 200 trial participants have been obtained, and/or 75 deaths have been documented during the trial. If the first interim analysis of 30-day mortality data is significant (*P* <0.001) for benefit or harm from the intervention, a second interim analysis will be made when 30-day mortality data of 300 trial participants have been obtained and/or an additional 25 deaths have been documented. If the second interim analysis is also statistically significant (*P* <0.001) for benefit or harm from the intervention the DMC can advise the steering committee to stop the trial.

### Statistical analysis

The outcome measures will be analysed for all randomised patients in a modified intention-to-treat analysis leading to the primary results of the trial [46]. Patients with the following major protocol violations will not be included in a per-protocol analysis: not fulfilling an inclusion criterion; fulfilling an exclusion criterion; IC for <48 h because of early discharge to the ward. The primary outcome measure, 30-day mortality, will be analysed with an unadjusted univariate logistic regression, and a multivariate logistic regression analysis will be made adjusting for stratification variables: trial-site, APACHE II score (10 to 14 or ≥15), and perforated viscera (yes *versus* no); and design variables: age, ASA score (1 to 2 or ≥3), cancer, and nature of surgery (+/− re-operation). The secondary outcome measure, survival within the total observation time, will be analysed with an unadjusted Cox regression analysis, and a Cox regression analysis adjusted for the above-mentioned stratification variables and design variables [47]. Survival within the total observation time will be illustrated with Kaplan-Meier estimates. Fisher’s exact or chi-squared tests will be used, depending on values, to analyse the differences of frequencies of registered complications in the two groups. Mortality data will be retrieved on patients registered as ‘not included in the trial due to lack of IC bed’. The data on these patients will be compared with that from the WC group, then included with the WC group data and compared with the IC group. Data on a semi-quantitative scale will be analysed using the Mann–Whitney test. Double sided *P* values <0.05 will be considered statistically significant.

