### Randomisation

The patients are randomised using a telephone-based central interactive-voice-response system managed by the Copenhagen Trial Unit (CTU). The randomisation system is accessible around the clock. It ensures immediate computer-based allocation, and adequate allocation concealment. A computer-generated block randomisation, with the investigators unknown and varying block size is used. Stratification variables are: trial site; APACHE II score (10 to 14 or ≥15); and perforated viscera (yes *versus* no).

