### Sample size

Emergency major abdominal surgical patients with an APACHE II score ≥10/11 have a 28% to 45% mortality rate [27-31]. We assume that patients with an APACHE II score of ≥10 have a 30-day mortality of 38%. We aim to confirm or reject an intervention effect of 13% absolute risk reduction in mortality (a relative risk reduction of 34%), in accordance with the difference between group mortality detected in our recent observational study of optimised perioperative care in perforated peptic ulcer patients [48]. The sample size with a type 1 error risk of 5%, and a type 2 error risk of 20% (80% power), was estimated to 200 patients in each group [49].

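### Two logistic regressions are planned for the primary outcome at the same 0.05 threshold, and the plan does not say which one decides

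*Protocol article*

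**What the plan says.** The Outcome measures section names a single primary outcome: "The primary outcome measure is all-cause 30-day mortality". For it, the Statistical analysis section gives two models: the outcome "will be analysed with an unadjusted univariate logistic regression, and a multivariate logistic regression analysis will be made adjusting for stratification variables" (site, APACHE II band, perforated viscera) together with age, ASA class, cancer and nature of surgery. One criterion covers all tests: "Double sided *P* values <0.05 will be considered statistically significant". The word primary is attached to the outcome and to the modified intention-to-treat results, but to neither model.

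Under Randomisation: "Stratification variables are: trial site; APACHE II score (10 to 14 or ≥15); and perforated viscera" (yes or no). The unadjusted model contains none of these three factors.

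Under Sample size, the trial is planned on the risk scale. It states "We assume that patients with an APACHE II score of ≥10 have a 30-day mortality of 38" per cent, and "We aim to confirm or reject an intervention effect of 13% absolute risk reduction in mortality (a relative risk reduction of 34" per cent). The size, per arm, follows: "The sample size with a type 1 error risk of 5%, and a type 2 error risk of 20% (80% power), was estimated to 200". The article names no effect measure for reporting the result.

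**The concern.** One primary question has two P values, each eligible to be called significant at 0.05, and there is no rule for the case where they differ. The two models do not estimate the same quantity: the unadjusted odds ratio is marginal, and the adjusted one is conditional on the covariates and normally lies further from 1. Disagreement is therefore to be expected in some trials. When it happens, a reader cannot tell from the article which result is the trial's answer on mortality.

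Two lesser matters follow. If the unadjusted model is taken as deciding, the variables used to balance the groups, and other predictors already collected, are left out of the primary test. And the target is an absolute and relative risk reduction, while a logistic coefficient is on the odds scale. At mortality of 25–38% the two scales are far apart.

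**Working it through.** **1. The plan's own sample size.** Inputs from the Sample size section: 38% against 25% (38 − 13), two-sided 5%, 80% power. With pooled variance and mean proportion 0.315:

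n = [1.960·√(2·0.315·0.685) + 0.842·√(0.38·0.62 + 0.25·0.75)]² / 0.13² = (1.288 + 0.547)² / 0.0169 ≈ 199.2, so 200 per group.

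The stated 200 is reproduced, and power at 200 is 80.1%. The size rests on an unadjusted comparison of two proportions. A Wald test in the unadjusted logistic model would need 203 per group (79.5% power at 200), so 400 patients still fits.

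**2. The target on each scale.**
- Risk ratio = 0.25/0.38 = 0.658, a relative reduction of 34.2%.
- Odds ratio = (0.25/0.75)/(0.38/0.62) = 0.544, a reduction in odds of 45.6%.
- The same odds ratio over the article's 28–45% mortality range:
  - at 28%, odds 0.389 × 0.544 = 0.2115, risk 17.5%, absolute reduction 10.5 points;
  - at 45%, odds 0.818 × 0.544 = 0.445, risk 30.8%, absolute reduction 14.2 points.

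**3. How the two models behave together.** The simulation had 400 patients, 7 × 2 × 2 = 28 strata and 4,000 trials per setting. Site shares came from enrolment to date (Trial status). Everything else about the covariates is assumed:
- blocks of 4 or 6;
- prevalences: APACHE II ≥15 50%, perforation 40%, ASA ≥3 55%, cancer 25%, re-operation 20%;
- log odds ratios at moderate strength: 0.7, 0.4, 0.7, 0.4 and 0.3 respectively, 0.6 per SD of age, and site effects between −0.3 and 0.3.

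All effects were also run at half and at one and a half times this strength. Mortality was calibrated to 38% in both groups (null) or 38% and 25% (planned effect). Rejection rates are in per cent.

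| Covariate strength | Null: unadjusted | Null: adjusted | Null: either | Effect: unadjusted | Effect: adjusted | Effect: disagree |
|---|---|---|---|---|---|---|
| 0.5× | 5.08 | 5.75 | 6.55 | 81.35 | 82.53 | 4.43 |
| 1× | 4.75 | 5.88 | 7.05 | 80.38 | 85.33 | 7.75 |
| 1.5× | 3.93 | 4.98 | 6.60 | 80.60 | 89.05 | 10.55 |

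- Power difference: 82.53 − 81.35 = 1.2, 85.33 − 80.38 = 5.0 and 89.05 − 80.60 = 8.5 points.
- Direction of disagreement at 1×: either model is significant in 86.73%. So only the adjusted model is significant in 86.73 − 80.38 = 6.35%, and only the unadjusted in 86.73 − 85.33 = 1.40%.
- Mean odds ratio at the planned effect: about 0.54 unadjusted; 0.52, 0.48 and 0.44 adjusted.

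Monte Carlo error is about 0.3–0.4 points for the null rates and 0.5–0.6 for power. Simulations with other assumed moderate effects gave either-model null rates of 6.7% and about 6%, disagreement of about 6%, and power of 81.2% against 84.7% (3.5 points) and 83% against 87% (4 points).

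**The case against.** The best defence is that both models and their covariates are fixed in advance, so nothing is invented later. The unadjusted model comes first and matches the sample-size method, and the steering committee sees no data until completion. An analysis plan that is not shown may rank the two. Most of this is true, but order of mention is not a designation. The article sets out the models, the covariates, most of the cut-points and the threshold, and leaves open only which model decides. The 6–7% applies only if either result may be claimed. The article does not say so, but does not exclude it. Part of the excess belongs to the adjusted Wald test itself (5.0–5.9% alone).

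Several stronger readings are tempting and are not supported:

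- **Unadjusted confidence intervals are too wide.** Not on the log-odds scale. In a check under the null, the mean standard error was 0.209 unadjusted and 0.225 adjusted, and the unadjusted value matched its sampling SD of 0.208. Adjustment gains power because the conditional odds ratio lies further from 1.
- **Planned power is lost.** The calculation took no credit for stratification, and the unadjusted test still delivers 80–81%.
- **APACHE II must be continuous.** Simulated power was 84.7% with the two bands and 85.4% with the score, which is not a material gain.
- **The plan reports only odds ratios.** It never says so. Risks can be derived from a logistic model.

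**Conclusion.** The point stands as a missing designation: two prespecified tests of one primary outcome, one threshold, and no statement of which decides. Under the assumed covariate effects, this allows a false-positive rate of about 6–7% if either may be claimed, and conflicting verdicts in roughly 4–11% of trials at the planned effect. Relying on the unadjusted model costs about 1 to 8 points of power relative to the adjusted one (3.5 to 5 at moderate strength). These figures depend on assumed prognostic strength. The power gain is a favourable case, because the adjusted model fitted in the simulation was the one that generated the data.

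A reader might infer that the unadjusted test is invalid or that the sample size is wrong. Neither follows: its type I error was 3.9–5.1%, and 200 per group reproduces. The difference between odds and risk scales affects how the result is read against the target, not the validity of the test. The change is worth making because a better-matched model is already in the plan.

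**What to change.** - Name the covariate-adjusted logistic model already listed as the single primary analysis of 30-day mortality, and state that its two-sided P value decides.
- State in advance how very small sites are pooled, with a numerical threshold. One site had 2 of the 199 patients enrolled at the time of writing (about 400 × 2/199 ≈ 4 at full size), so its own coefficient may not be estimable.
- Make the unadjusted model a sensitivity analysis, reported whatever it shows.
- From the primary model, report the standardised risk difference and risk ratio with 95% confidence intervals beside the odds ratio.

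The cost is wording. Every covariate is either a stratification factor or already in the planned adjusted model. With 199 of 400 patients enrolled and the steering committee without access to the dataset, the choice can still be fixed credibly before any results are seen. If an analysis plan already ranks the models, it is enough to confirm that and align the two documents.

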### Recruitment, screening and enrolment

We recruit patients postoperatively in the post-anaesthesia care unit and intensive/intermediate care unit. All adult patients who have undergone the relevant surgical procedures have a venous and arterial blood gas sample taken upon arrival from the operating theatre. Uniformity of trial site standard postoperative vital-sign monitoring is ensured, enabling calculation of the APACHE II score, when patients are ready to be transferred to the surgical ward in accordance with the trial site’s discharge criteria - local adjusted versions of the Danish national recommendations [33] (Additional file 2: National discharge recommendations). At this point of time the attending anaesthetist screens for trial eligibility using a standard screening form with flowcharts (Figure 1). If none of the exclusion criteria 1 to 7 apply, the APACHE II score is calculated from the worst parameter values measured 12 h preoperatively, peroperatively, and up to 12 h postoperatively. If there is missing data for the APACHE II score calculation, when the patient is transferable to the ward, current values are used. GCS score, blood pressure and heart rate recorded during anaesthesia are not included in the APACHE II score calculation. The APACHE II score is calculated electronically on the InCare trial website [34]. If the patient has an APACHE II score of ≥10 the anaesthetist checks that an IC bed can be established at the intermediate care, intensive care or post-anaesthesia care unit. If an IC bed is not available, the patient is registered as ‘not included due to lack of IC bed’ and transferred to the ward. If an IC bed is available, written consent is obtained from the patient or a legal representative, if the patient is incapable. If it is not possible to contact a legal representative within 2 h, the patient is included in the trial, and written consent is obtained as soon as possible.

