### Previous research

The effect of postoperative IC is unresolved in high-evidence studies. Previous studies of IC have been non-randomised, observational or descriptive, often with contradictory results [17-23]. Davies *et al*. and Bellomo *et al*. [18,19] found no reduction in postoperative in-hospital mortality or morbidity following introduction of an IC unit at their facilities. Both studies reported a change in surgical intake tending more to emergency surgery after introduction of the IC unit. This may explain the lack of effect in their unadjusted analyses. Turner *et al*. [20] found an excess crude mortality rate in patients not admitted to IC units despite requests from the attending surgeon or anaesthetist. In a similar design McIlroy *et al*. [21] concluded that IC may lead to longer hospital stay, but no effect on 30-day mortality or all-cause morbidity could be shown. Jones *et al*. [22] compared two hospitals (one with, and one without, an IC unit). This study suggested that postoperative IC might reduce cardiopulmonary complications after major abdominal surgery, when risk adjusting with Physiologic and Operative Severity Score for the enumeration of mortality and morbidity (POSSUM score). No effect on mortality or length of hospital stay could be shown. Swart *et al*. [23] compared postoperative intensive care with surgical ward care in colorectal surgical patients with a preoperative anaerobic threshold <11 mL oxygen/ kg/min. They found that there was significant decrease in cardiac adverse events in the intensive care patients, but no effect on in-hospital mortality, or length of hospital stay could be shown.

Common in the previous research is a high risk of bias as confounding by indication and selection bias, and thereby unbalanced number of risk patients in the compared groups is imminent. Furthermore, the cited studies are characterised by limited power to show effect on mortality, because they predominantly investigate patients undergoing scheduled surgical procedures which have much lower mortality than emergency abdominal surgical procedures.

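### The supplementary analysis that adds patients turned away for lack of an IC bed to the randomised ward arm gives an IC v ward mortality contrast that randomisation does not protect and that may be biased in either direction

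*Protocol article*

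**What the plan says.** Lack of an IC bed is exclusion criterion 8. Under Recruitment, screening and enrolment, the bed check comes after exclusions 1 to 7 and after the APACHE II threshold. The text continues: "If an IC bed is not available, the patient is registered as" not included for that reason, and goes to the ward. Consent is sought only when a bed is available, so these patients are neither asked for consent nor randomised.

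The Statistical analysis section bases the primary results on a modified intention-to-treat analysis of randomised patients. Later it says that mortality will be retrieved for the turned-away patients and compared with that of the WC group, and that they are "then included with the WC group data and compared with the IC group". No condition links the two steps, and the pooled comparison is not called exploratory or a sensitivity analysis. The only significance rule given is general: "Double sided *P* values <0.05 will be considered statistically significant".

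**The concern.** The pooled control group mixes randomised ward patients with a non-randomised cohort, while the IC arm stays purely randomised. The text shows three ways in which that cohort can differ from both randomised arms:

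- **Bed pressure.** These patients arise only when no bed can be established in intermediate care, intensive care or post-anaesthesia care. According to the Ward care section, ward patients who deteriorate are moved to intermediate or intensive care, so full units could affect their outcome directly. Every IC patient comes from a time when a bed was free.
- **Consent.** The randomised arms are filtered by consent; the turned-away patients are not.
- **Ward care received.** The protocol-based discharge note is described for patients allocated to WC. It is not stated for turned-away patients.

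Adjustment may not be able to repair this. Under Baseline data, covariates such as ASA score and cancer are registered after inclusion, and for turned-away patients the article promises only mortality. Trial site and APACHE II score should be known from screening.

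The result would be a second IC v ward mortality comparison, with a larger control group than the randomised one and read against the same P threshold. Any mortality difference linked to bed shortage would be attributed to IC. The article itself faults earlier IC research for "confounding by indication and selection bias" and presents this trial as the lower-bias alternative.

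**Working it through.** **Inputs from the Sample size section:** WC mortality 38%; absolute reduction 13 points, so 25% in IC; two-sided alpha 5%; power 80%; 200 per group. The same section cites a 28% to 45% mortality range for patients above the APACHE II cut-off.

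**Assumptions:** the article gives neither the number (m) nor the mortality (q) of turned-away patients. I take m = 50 to 400, and use the two ends of the cited range for q.

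**Step 1: the plan's own figure.** Normal approximation, pooled variance under the null, mean proportion (0.38 + 0.25)/2 = 0.315:

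n = [1.96·√(2·0.315·0.685) + 0.8416·√(0.38·0.62 + 0.25·0.75)]² / 0.13² = (1.288 + 0.547)² / 0.0169 ≈ 199.2, rounded up to 200 per group.

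This matches the plan. Power at 200 per group is 80.1%.

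**Step 2: pooled test with no true IC effect.** Both randomised arms have 38% mortality.

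- Pooled control mortality: pc = (200·0.38 + m·q)/(200 + m). Spurious difference: d = pc − 0.38.
- Null standard error: SE0 = √[p̄(1 − p̄)(1/200 + 1/(200 + m))], where p̄ is overall mortality.
- True standard error: SE1 = √[0.38·0.62/200 + (200·0.38·0.62 + m·q(1 − q))/(200 + m)²].
- P(false benefit) = Φ[(d − 1.96·SE0)/SE1]. For false harm, replace d with −d.

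Example, m = 100 and q = 0.45: pc = (76 + 45)/300 = 0.403; d = 0.0233; p̄ = 197/500 = 0.394; SE0 = 0.0446; SE1 = 0.0445. So (0.0233 − 0.0874)/0.0445 = −1.44, and Φ(−1.44) = 7.5%.

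Example, m = 100 and q = 0.28: pc = (76 + 28)/300 = 0.347; d = −0.0333; p̄ = 180/500 = 0.36; SE0 = 0.0438; SE1 = 0.0439. So (0.0333 − 0.0859)/0.0439 = −1.20, and the chance of false harm is 11.6%.

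| m | q = 45%: spurious benefit (points) | q = 45%: P(false benefit) | q = 28%: spurious harm (points) | q = 28%: P(false harm) |
|---|---|---|---|---|
| 50 | 1.4 | 4.8% | 2.0 | 6.4% |
| 100 | 2.3 | 7.5% | 3.3 | 11.6% |
| 200 | 3.5 | 12.6% | 5.0 | 22.9% |
| 400 | 4.7 | 20.9% | 6.7 | 41.3% |

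The nominal value in each direction is 2.5%. It is kept when q equals the WC mortality of 38%.

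**Step 3: pooled test when the planned effect is real (38% v 25%).** With q = 28%, power falls from 80.1% to about 63% (m = 100) or 52% (m = 200). With q = 38%, it rises to about 87% or 90%. That rise is the attraction of pooling, and it depends on an equality that the design does not secure.

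**Step 4: the preliminary comparison as a safeguard.** Power of turned-away (45%) v WC (38%, n = 200) is 15%, 21%, 29% and 37% for m = 50, 100, 200 and 400. A non-significant result would be the likely outcome even with a difference large enough to cause the bias shown in Step 2.

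**The case against.** The strongest reply is that this analysis decides nothing. The primary results come from randomised patients. The pooled comparison appears late in the section, belongs to no listed outcome or hypothesis, and enters neither the sample size nor the interim rules. That stands, and it limits the severity. A reader might infer from the pooling sentence that the trial's randomised comparison is itself broken; the text does not support this.

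Three further replies also stand:

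- **Direction.** A reader might infer that pooling favours IC. Nothing in the article says whether turned-away patients die more or less often than WC patients, so false harm or a masked benefit is as open as a false benefit.
- **Comparability.** Turned-away patients have passed exclusions 1 to 7 and the APACHE II threshold and are ready for the ward. They are probably closer to the WC arm than controls chosen on clinical indication would be. The consent filter is also not uniform, because a patient may be included first when no representative is reached within 2 h.
- **Earlier studies.** A reader might infer that the article condemns this very design. Under Previous research it describes one study of patients not admitted to IC despite clinicians' requests and another of similar design, within a general criticism of bias. It does not say that bed shortage was the reason for non-admission.

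Differences by site or calendar time are plausible, but the article gives no data on them. A full protocol or analysis plan might label or adjust the analysis. Even so, the article states the pooling explicitly, and similarity on eligibility criteria does not replace random allocation.

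**Conclusion.** The point holds as a moderate defect confined to a supplementary analysis. As written, the plan produces an IC v ward mortality contrast whose control group is partly non-randomised, with no label and no separate rule for interpreting it. With no true effect and 38% mortality in both randomised arms, 100 to 200 turned-away patients raise the chance of a false finding in one direction from 2.5% to 7.5–12.6% (benefit, at 45% mortality) or 11.6–22.9% (harm, at 28%). These figures illustrate size only: they rest on assumed numbers and mortality for the turned-away patients and on a normal approximation. The primary analysis and the sample size need no change.

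**What to change.** Remove the pooled comparison with IC. Report the 30-day mortality of the turned-away patients with a 95% confidence interval beside the WC arm, by site and APACHE II stratum, as a description of external validity. State that every IC v WC inference comes from randomised patients only.

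If the pooled result is kept, label it non-randomised and exploratory, adjust it at least for site and APACHE II score, and draw no efficacy conclusion from it.

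The change takes a sentence or two in the Statistical analysis section. It needs no more patients and gives up only an apparent gain in precision that randomisation does not support.
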